## Abstract

**Background:**

Magnetic Resonance Imaging (MRI) of patients with implanted cardiac devices is currently considered hazardous due to potential for electromagnetic interference to the patient and pacemaker system. With approximately 60 million MRI scans performed worldwide per year, an estimated majority of pacemaker patients may develop an indication for an MRI during the lifetime of their pacemakers, suggesting that safe use of pacemakers in the MRI environment would be clinically valuable. A new pacing system (Medtronic EnRhythm MRI™ SureScan™ and CapSureFix MRI™ leads) has been designed and pre-clinically tested for safe use in the MRI environment. The EnRhythm MRI study is designed to confirm the safety and efficacy of this new pacing system.

**Methods:**

The EnRhythm MRI study is a prospective, randomized controlled, unblinded clinical trial to confirm the safety and efficacy of MRI at 1.5 Tesla in patients implanted with a specifically designed pacemaker and lead system. The patients have standard indications for dual chamber pacemaker implantation. Successfully implanted patients are randomized in a 2:1 ratio to undergo MRI (MRI group) or to have no MRI scan (control group) at 9–12 weeks after pacemaker system implantation. Magnetic resonance (MR) scanning includes 14 head and lumbar scan sequences representing clinically relevant scans while maximizing the gradient slew rate up to 200 T/m/s, and/or the transmitted radiofrequency (RF) power up to SAR (specific absorption rate) levels of 2 W/kg body weight (upper limit of normal operating mode). Full interrogation of all device information and sensing and capture function are measured at device implantation, every follow-up and before and immediately after MRI in the MRI group and at the same time points in the control group. Complete pacemaker and lead evaluations are also done at one week and one month after the scan for the MRI and control group patients.

The primary endpoint is safe and successful completion of the MRI scan as measured by freedom from both MRI-procedure related complications and clinically significant changes in the sensing and capture function of the leads.

**Results:**

Results will be communicated after approximately 156 and 470 patients have completed 4 months of follow-up.

**Trial Registration:**

ClinicalTrials.gov identifier: NCT00433654.

## Background

Magnetic Resonance Imaging (MRI) of patients with pacemakers and other implanted devices is presently contraindicated, because of the potential hazards of this diagnostic method on active implants [1]. However, there is an increased need for MRI in these and other older patients [2]. With approximately 60 million MRI scans performed worldwide per year, an estimated majority of pacemaker patients may be indicated for an MRI during the lifetime of their pacemaker, suggesting that safe use of pacemakers in an MRI environment would be clinically valuable.

Several studies report that a small number of pacemaker patients underwent MRI scanning under controlled situations and by taking certain precautions. This was only done if the risk-benefit ratio was considered acceptable. Still, scanning pacemaker patients in an MRI is not without risk. Six non pacemaker-dependent patients died in Germany during an MRI examination that took place without any monitoring. In three of these cases, there was suggestive evidence that death may have been due to induced ventricular fibrillation [3]. Other studies have shown that pacing thresholds increased significantly from pre- to post-MRI examination [4,5]. Furthermore, animal testing has demonstrated that the temperature at the lead tip increased up to 20°C during MRI scanning of the heart [6], which could result in tissue damage.

Pacemaker systems can be designed to limit the potential risks of MRI for patients. Such a design has been realised, prompting a clinical trial to test its function with and without MRI. Since all available pacemaker systems are currently contraindicated for use during MRI, the new pacing system consisting of the EnRhythm MRI™ SureScan™ pacemaker and CapSureFix MRI™ Model 5086 leads are evaluated for safe use in the MRI environment. This pacing system is a modified version of the commercially available EnRhythm^® ^pacemaker and CapSureFix^® ^Novus Model 5076 leads. The design of the study evaluating this pacemaker system is reported in this paper.

Pacemaker design enhancements were made to minimize the energy induced on leads and discharged at electrodes. Hardware changes were made to ensure reliable operation while MRI is active. Leads were altered to reduce lead tip heating from radiofrequency (RF). Radiopaque labels are present on the lead and device to indicate that a system is implanted that can be used in the MRI. Furthermore, the pacemaker can be programmed to the MRI SureScan mode to permit appropriate function during MRI scanning. In this mode, the physician can choose either to programme an asynchronous pacing mode or a non-pacing mode. Asynchronous pacing will maintain appropriate pacing support throughout the MRI examination regardless of the noise induced on the pacing system. For those patients that are non-pacemaker dependent, the non-pacing mode is available. Diagnostic data collection, automatic system monitoring measurements, atrial arrhythmia detection and atrial arrhythmia therapy are suspended during MRI SureScan mode operation. Furthermore, before programming the MRI mode, the system reinforces the physician to check carefully the safety requirements necessary for the pacemaker patient to receive an MRI examination.

## Study design

This study is a prospective, randomized controlled, unblinded, multi-center investigational trial and is being conducted in approximately 75 centers in the United States (US), Canada, Europe and Middle East. After implantation of the Medtronic EnRhythm MRI SureScan system (Medtronic EnRhythm MRI™ SureScan™ pacemaker and Medtronic CapSureFix MRI™ leads), patients are required to have follow-up visits at 2 months, 2.5 months (between 9–12 weeks post-implant an MRI scan or no-MRI scan is performed, depending on randomization), 3 months (1 week post- MRI/no-MRI) and 4 months post-implant (1 month post-MRI scan/no-MRI). Further follow-up is required at 6 months post-implant and every 6 months thereafter until the study ends. Full interrogation of all device information and impedance, sensing and capture function are measured at implant, every follow-up and immediately before and after MRI in the MRI group and at the same time points in the control group. The system must be implanted for more than 6 weeks to allow the Implantable Pulse Generator (IPG) and leads to develop stable pacing and sensing function in the patient prior to allowing the patient to undergo an MRI scan.

A concurrent control group design was selected because the effect of MRI on capture and sensing measurements is unclear. The observed effect in this study will theoretically result from the sum of the natural variation in capture and sensing parameters common to all patients, added to the effect of the MRI examination. Without a randomized control group, it is impossible to isolate the effect of the MRI from the component common to all patients with an IPG system. The possible difference in the electrical measurements due to the MRI scan is precisely what study investigators wish to understand.

### Inclusion/exclusion criteria

The following in-/exclusion criteria are used. Criteria were primarily chosen to comply with the labeling of the pacemaker system.

#### Inclusion Criteria

• Patients who have a Class I or II indication for implantation of a dual chamber pacemaker according to the American College of Cardiology (ACC)/American Heart Association (AHA)/Heart Rhythm Society (HRS) guidelines [7].

• Patients must be able to undergo pectoral implantation.

• Patients who are able and willing to undergo elective MRI scanning without sedation (anxiolysis permitted).

• Patients who are geographically stable and available for follow-up at the study center for the length of the study.

#### Exclusion Criteria

• Patients who require a legally authorized representative to obtain consent.

• Patients with a mechanical tricuspid heart valve

• Patients with tricuspid valve disease including valve replacement.

• Patients for whom a single dose of 1.0 mg Dexamethasone acetate may be contraindicated.

• Patients who have a previously implanted pacemaker or an implanted cardioverter/defibrillator. Those who have abandoned pacemaker/ICD leads are excluded; however, patients with complete system explantation may be included.

• Patients who require an ICD rather than a pacemaker.

• Patients currently indicated, or for whom an indication is anticipated, to undergo another MRI procedure other than those specifically described in the study during the period of follow-up required by the study.

• Patients with previously implanted active medical devices (other than those stated above).

• Patients with non-MRI compatible devices (those above and others such as neurostimulators) or implanted material (e.g. non-MRI compatible sternal wires, biostimulators, metals or alloys).

• Patients with medical conditions that preclude the testing required by the protocol or limit study participation.

• Patients who are enrolled in or intend to participate in another clinical trial (of an investigational drug or device, new indication for an approved drug or device, or requirement of additional testing beyond standard clinical practice) during this clinical trial.

• Pregnant women, or women of childbearing potential and who are not on a reliable form of birth control.

• Patients with exclusion criteria required by local law (e.g age, breast feeding).

### Pacemaker implantation and measurements

The devices to be implanted are the model 5086 MRI CapSureFix^® ^active fixation leads for both right atrium and right ventricle. Typically right or left pectoral approaches via the subclavian, axillary or cephalic veins are used to introduce the leads, which are then advanced to the investigators' choice of location in the heart to sense and capture the atrial and ventricular myocardium. The EnRhythm MRI SureScan IPG is connected to the leads in the pectoral site.

After implantation, measurements of voltage stimulation thresholds at 0.2 and 0.5 ms pulse duration, impedance and sensing amplitudes measurements are taken in both the atrium and ventricle. The investigator completes a questionnaire concerning handling characteristics of the leads during implantation.

Measurements at the time of MR scanning are described below. Further sets of measurements of pacemaker function are made at every required follow-up visit.

### Randomization

Patients were originally planned to be randomized in a 1:1 ratio, but later during the trial the ratio was modified to a 2:1 ratio to undergo an MRI scan (MRI group) or not to undergo an MRI scan (control group) after a successful implantation of an EnRhythm MRI SureScan pacing system (Figure 1). It is anticipated that more than 60% of the implanted patients will be randomized in a 1:1 order and the remainder in a 2:1 order. The ratio was adjusted so as to meet regulatory requirements for the minimum number of patients scanned.

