#### a) Primary Objectives

1. To assess if the MRI-related complication-free rate in the month following MRI is greater than 90%. A one-sided exact test with a 97.5% confidence interval is used for analysis.

2. To compare the changes in a) atrial and b) ventricular voltage thresholds at 0.5 ms before and one month after MRI/no-MRI between the MRI and control groups. The hypothesis will test whether the proportions of patients (p_1_and p_2_) that experience an acceptable threshold increase less or equal to 0.5 V are equivalent (Δ = 10%, p_1 _and p_2 _= 96%) between the two groups. The objective will be analyzed using a two-sample 97.5% confidence interval, with p-values from the Farrington-Manning test for equivalence of proportions.

3. To compare the changes in a) atrial and b) ventricular sense amplitudes before and one month after MRI/no-MRI between the MRI and control groups. The hypothesis will test whether the proportions of patients (p_1 _and p_2_) who experience a sense amplitude decrease less than 50% and whose sense amplitudes remain above an clinically acceptable minimum (1.5 mV for atrium and 5 mV for the ventricle) at one month post-MRI/no-MRI are equivalent (Δ = 10%, p_1 _and p_2 _= 93%) between the two groups. The objective will be analyzed using a two-sample 97.5% confidence interval, with p-values from the Farrington-Manning test for equivalence of proportions.

All 3 primary objectives of this second set need to be met in order to pass the study.

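### The second-analysis capture and sensing comparisons name an unstratified test although allocation moved from 1:1 to 2:1 mid-trial; a small, avoidable part of any between-period difference enters the MRI-control contrast

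*Protocol article*

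**What the plan says.** All references are to the protocol article.

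- **Randomization.** The trial began with 1:1 allocation; "later during the trial the ratio was modified to a 2:1 ratio to undergo an MRI scan (MRI group") or no scan. The expected mix is that "more than 60% of the implanted patients will be randomized in a 1:1 order and the remainder in a 2:1 order". The stated reason is external: "The ratio was adjusted so as to meet regulatory requirements for the minimum number of patients scanned".
- **a) Primary Objectives, second analysis (470 patients), objectives 2 and 3.** The proportions of patients with an acceptable capture threshold change and an acceptable sensing amplitude are compared between groups. The margin is 10 points and the planned rates are 96% (capture) and 93% (sensing). The method for each objective is the same: "The objective will be analyzed using a two-sample 97.5% confidence interval, with p-values from the Farrington-Manning test for equivalence of proportions". No stratum is named.
- **Sample size and data use for analysis.** The largest requirement in the second set is 122 per group, at alpha 0.025 and at least 80% power. This section lists analysis exclusions and a visit-window sensitivity analysis, but nothing on allocation period.
- **Abstract, Methods.** "Successfully implanted patients are randomized in a 2:1 ratio to undergo MRI (MRI group) or to have no MRI scan (control group"). The 1:1 period is not mentioned.

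**The concern.** Randomisation makes the groups comparable within each allocation period. When two periods with different ratios are merged, the groups have different period mixes, so a difference in success between the periods passes in part into the crude MRI-control difference. The named method is a plain comparison of two proportions; followed as written, it merges the periods.

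The section Study design justifies the control group as the means of separating the MRI effect from variation common to all paced patients. Merging the periods weakens that separation a little. The direction matters: if success rises later, for instance with a changing mix of centres or growing experience, the bias favours the MRI group, which is the less safe direction in a study meant to confirm safety.

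**Working it through.** **Inputs.** From the article: N = 470; more than 60% at 1:1 and the rest at 2:1; margin 10 points; planned rates 96% and 93%; alpha 0.025; 122 per group. Assumed: the drift, meaning the success rate in the 2:1 period minus that in the 1:1 period, taken as equal in both groups. The documents give no value for it.

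**1. The plan's own sample size.** Farrington-Manning for sensing, equal groups, no strata, one-sided 0.025, 80% power. The restricted estimates at the margin are 0.8556 and 0.9556.

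n = [1.960 × √(0.8556×0.1444 + 0.9556×0.0444) + 0.842 × √(2×0.93×0.07)]² / 0.10² = (0.799 + 0.304)² / 0.01 ≈ 121.5, so 122 per group.

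This reproduces the stated figure. The calculation is therefore consistent with an unstratified, equal-allocation comparison at one-sided 0.025.

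**2. Period mix at the 60/40 boundary.**
- 1:1 period: 0.6 × 470 = 282, so 141 MRI and 141 control.
- 2:1 period: 188, so 125.3 MRI and 62.7 control.
- Totals: 266.3 MRI and 203.7 control, a ratio of 1.31:1.
- Late share: 125.3/266.3 = 47.1% of MRI and 62.7/203.7 = 30.8% of control. Gap: 16.3 points.

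The gap is 14.1 points at 70/30 and 10.7 at 80/20. Because the article says more than 60%, 16.3 is the upper end.

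**3. Bias of the crude difference** = gap × drift.

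| Assumed drift | Bias at 60/40 | Bias at 80/20 |
|---|---|---|
| 2 points | 0.33 | 0.21 |
| 5 points | 0.81 | 0.54 |
| 10 points | 1.63 | 1.07 |

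A bias equal to the whole margin would need a drift of 10/0.163, about 61 points.

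**4. Ceiling on upward drift from the planned rates.** If late success were 100% and controls averaged the planned rate, early success would be (rate − 30.8)/0.692.
- Capture: (96 − 30.8)/0.692 = 94.2%, so a drift of at most about 5.8 points and a bias of about 0.9 points.
- Sensing: (93 − 30.8)/0.692 = 89.9%, so a drift of at most about 10.1 points and a bias of about 1.6 points.

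**5. Error rate when the true difference lies exactly at the margin** (93% control, 83% MRI, N = 470, 60/40). SE = √(0.83×0.17/266.3 + 0.93×0.07/203.7) = 2.91 points. The one-sided error is the normal tail beyond 1.96 − bias/SE.
- Success improves later by 2 or 5 points: 3.2% or 4.6% instead of 2.5%; at 10 points, about 8%.
- Success worsens later by 2, 5 or 10 points: 1.9%, 1.3% or 0.6%.
- With only 244 evaluable patients and a 5-point improvement: 3.9%.

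**6. Cost of stratifying** (93% in both groups).
- Pooled: SE = √[0.0651 × (1/266.3 + 1/203.7)] = 2.38 points.
- Mantel-Haenszel: the weights are 141×141/282 = 70.5 and 125.3×62.7/188 = 41.8, so SE = √(0.0651/112.3) = 2.41 points.
- The variance ratio is 1.028. The evaluable number needed rises from about 249 (pooled, with the unequal overall ratio) to about 256.

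**The case against.** The strongest reply is that no sentence says the periods are merged or that period is ignored. This is a condensed article; it refers to a separate investigational plan, and neither that plan nor the analysis plan is shown. Either could add a stratum or a sensitivity analysis. This stands as a limit on what can be claimed, but it does not dispose of the point: the article names a specific test, and that test has no stratum.

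The second reply is about size, and it largely stands. Drift is undocumented, and high planned rates leave little room for improvement. Both endpoints include a within-patient change, so stable shifts in level largely cancel; the absolute minimum amplitudes in the sensing endpoint are only a partial exception. Unresolved dislodgements, unstable pre-MRI thresholds and capture data without strip documentation are excluded rather than counted as failures, which removes several routes by which experience or documentation could act.

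A reader might infer more than the article supports:
- **That any drift over time is confounded with MRI.** Drift within a period is balanced by randomisation; only the between-period difference leaks, and at most about 16% of it.
- **That the whole primary analysis is affected.** Objective 1 of the second analysis is an MRI-related complication-free rate with no between-group contrast. The 156-patient analysis probably lies wholly in the 1:1 period, since that period covers more than 282 patients if enrolment is sequential.
- **That the ratio was changed in response to outcomes.** The stated reason is a regulatory minimum number of scans.
- **That the abstract's 2:1 undermines the analysis.** It is incomplete, but the 122 per group reproduces with equal allocation, and the body discloses the change.

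**Conclusion.** The point holds in a limited form. For second-analysis objectives 2 and 3, the named test does not fit the stated change in allocation. If it is followed as written, between about 11% and 16% of any between-period difference in success (for 80% down to 60% of patients at 1:1) enters the MRI-control difference. The bias is probably below about 1 point against a 10-point margin. Error control at the margin can move noticeably, but only if the true difference lies there and success improves later; if success worsens, the test becomes conservative.

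This rests on an assumed drift, on equal drift in both groups, on the one-sided 0.025 reading that reproduces 122 per group, and on the full plan not already stratifying. It is a worthwhile, inexpensive improvement and not a threat to the trial's validity.

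**What to change.** - For capture and sensing in the 470-patient analysis, replace the plain two-sample comparison with one stratified by allocation period (1:1, 2:1). A stratified Miettinen-Nurminen or Farrington-Manning score interval, or a Mantel-Haenszel risk difference, would serve, judged against the same 10-point margin.
- Apply the same stratum to the 156-patient analysis only if any of those patients were randomised after the change.
- If the full plan already stratifies, bring the article's method sentence into line with it.
- Editorially, have the abstract give both ratios and the expected mix.

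The cost is a change of wording and about 2.8% more variance. The roughly 256 evaluable patients then needed lie well inside 470. No design change is involved.

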**Figure 1 F1:**
[figure not shown]
Study visit flowchart.

### MRI scanning

Patients randomized to receive MR scanning undergo imaging at 9–12 weeks after implantation. Fourteen clinically relevant brain and lumbar spine MR scans are performed in each patient of the MRI group (total MRI investigation time of approximately 45 minutes, total active MRI scan time of approximately 30 minutes). According to the labelling of the MRI SureScan Pacing system, all MRI studies are performed at a 1.5 Tesla system, the slew rate ("gradient dB/dt") of the gradient system of each individual MR sequence is restricted to 200 T/m/s and the radiofrequency exposure of each individual MR sequence is restricted to a specific absorption rate (SAR) of 2 W/kg body weight or less. Furthermore, labelling requires that the isocenter of the RF coil falls above the first cervical vertebral body (C1) or below the twelfth thoracic vertebral body (T12). The sequences to be used were carefully chosen by the study's Scan Advisory Committee to be clinically applicable and similar between different commercially available 1.5 T closed bore MRI scanners (manufacturers GE, Siemens, Philips) and to include sequences utilizing high gradient slew rates and/or producing high SAR close to the labelling limits of the pacemaker system. Some of the MR scan protocols with already high gradient slew rates were modified to maximize the gradient exposure up to the system limit or if possible to 200 T/m/s. In addition, to maximize gradient exposure in the lumbar spine scans, the patient is placed in such a way (i.e., isocenter of the RF coil is at L1 and S1) that the highest induced voltages at the pacing system site are expected. At least one lumbar spine scan should achieve high SAR values. Validation of all scans is required by each center prior to executing the first study patient scan in order to ensure scan protocols for each particular site are comparable across sites.

At minimum, patients are continuously monitored via pulse oximetry during the scans. Verbal communication also takes place to assess or confirm any significant clinical changes. Voltage stimulation thresholds, sensing amplitudes and impedance, will be measured in both the atrium and the ventricle immediately before the MRI scans are started and immediately after the MRI scans are completed.

Although the clinical study includes a fixed set of brain and lumbar spine sequences, the MRI scanning requirements of the EnRhythm MRI pacing system makes it possible to perform diagnostic MRI scans of the anatomic region within C1 and T12 while placing the isocenter of the RF coil outside of this zone by changing certain MRI parameters.

